### Recruitment {15}

The managing director of all RAC facilities in the specific municipality will receive both written and oral information about the project and provide approval to initiate the study. Subsequently, the operation managers of the RAC facilities will receive oral information about the project and be asked to select three RAC facilities that meet the eligibility criteria for inclusion in the study. Ward managers at the selected RAC facilities will also receive information and participate in the staff training.

During a regular meeting for all residents in the somatic wards at the respective RAC facilities, members of the research team will provide verbal information about the project. Additionally, all potential residents will receive written information, including details about the Re-RAC intervention and study-specific aspects such as study goals, duration, participant roles, randomization, potential risks, voluntariness, and the written consent process. A few days after the information session, a research team member will visit each resident for an individual follow-up, address any questions, offer to read the information aloud if necessary, and ask whether the older adult wishes to participate. Those who express interest will provide written consent, after which eligibility screening will be conducted. We anticipate recruiting the participants over an 18-month period and the recruitment progress will be monitored monthly at research team meetings. If recruitment is slower than expected, contingency plans include extending the recruitment period or engaging additional facilities.

Nursing assistants who support participants in the intervention, along with rehabilitation staff and registered nurses at each participating ward, will receive both oral and written information during a ward meeting and be invited to participate as staff informants in focus-group interviews. Participating in the focus-group interviews is voluntary, but the staff are required to provide support for the intervention as part of their daily work.

## Assignment of interventions, allocation

### Sequence generation {16a}

Eligible participants will be randomized 1:1 to either treatment as usual (TAU) with Re-RAC as an add-on intervention or TAU alone, stratified by center (RAC facility). A computer-generated randomization sequence will be created using randomized permuted blocks of varying sizes.

### Concealment mechanism {16b}

To ensure allocation concealment, center-specific randomization lists will be prepared and distributed individually in sealed and sequentially numbered envelopes to the researcher responsible for the participant recruitment. These envelopes will be kept in a secure location and opened only after participant consent and screening have been completed.

### Implementation {16c}

The randomization sequence will be generated by the external statistician, who will not be involved in participant recruitment, enrollment, or assessment. A research team member will be responsible for enrolling participants and assigning them to interventions by opening the next envelope in sequence, following eligibility confirmation and consent.

## Assignment of intervention: blinding

### Who will be blinded {17a}

This study evaluates an intervention in which participants from both allocation groups may reside in the same ward, making it impossible to blind either the participant or the staff to their group assignment. Additionally, the nature of the intervention, which includes a training component delivered by the staff, precludes blinding for these groups. However, all researchers, except one, will remain blinded during the analyses. The unblinded researcher will be responsible for administering, collecting, and securely storing the coded data. This researcher will also be involved in the data collection and delivery of the intervention and therefore cannot be blinded to the randomization or the participants’ study IDs. Data entry into the electronic case report form (e-CRF) system called Greenlight Guru Clinical (GGC) will be performed by the unblinded researcher. Study ID numbers will remain concealed from the rest of the research team during the analyses. Outcome assessors and analysts, apart from the designated unblinded researcher, will remain blinded to group allocation. Statistical analyses will be conducted by an external, blinded statistician.

### Procedure for unblinding if needed {17b}

If any researcher is accidentally unblinded, they must not perform any tasks requiring blinding. Any instance of unblinding must be documented in a deviation log. All participant responses will be linked to a numerical pseudonym. In cases where unblinding becomes necessary, such as during an AE, the coding key may be accessed to identify the participant. 

## Data collection and management

### Plans for assessment and collection of outcomes {18a}

Following the eligibility screening, all participants will undergo the baseline assessment and wear an accelerometer for one week. The baseline assessment will be conducted using several questionnaires. To address potential challenges related to low vision and to reduce cognitive load, the questionnaires will be administered in an interview format. Additionally, the older adults will be advised to use their regular hearing and vision aids during all assessments, including MMSE-SR.

At the end of the intervention period, a follow-up assessment will be conducted, mirroring the baseline assessment. In conjunction with the follow-up, a proxy assessment of the older adults’ occupational performance (COPM-P) will be carried out by the OT at the RAC facility (Table 1).

To collect data on participants’ experiences, semi-structured individual interviews will be conducted with participants from the intervention group. Staff experiences will be collected through focus-group interviews after supporting at least one participant in the intervention.

Additionally, data on adherence, healthcare consumption, incidents, and medication use will be extracted from medical records and administrative systems for a period of 3 months before baseline and 3 months after the intervention concludes.

Any deviations from the study protocol or participant discontinuations will be documented.

### Measures

#### Canadian Occupational Performance Measure (COPM)

The COPM [43] is an interview-administered instrument used to assess occupational performance (COPM-P) and satisfaction with performance (COPM-S) for up to five self-determined activity issues in the areas of self-care, productivity, and leisure. Participants will rate their performance of and satisfaction with their highest-priority activity on a scale of 1–10, where 1 = unable to perform at all/not satisfied at all, and 10 = able to perform extremely well/extremely satisfied [42, 43].

The COPM has been used with individuals of various ages, diagnoses, and backgrounds and its psychometric properties are well established [43, 48, 49]. To validate the participants’ self-assessment of the performance (COPM-P), a proxy assessment will be conducted by an OT.

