##### Implementation of the intervention.

The intervention begins with an interview using the COPM [42, 43]. A researcher conducts the interview with the ward’s OT as an observer. The OT is present to understand the goal-setting process, as they will supervise the nursing assistants during the intervention. The OT will also contribute expertise related to participation in everyday life when formulating a measurable and realistic goal, within the relevant time frame.

During the interview, the older adult is asked to describe their daily life, including its activities and their performance, considering both the present and the past. The interview focuses on identifying both what works well and the challenges faced in daily life. Subsequently, the participant identifies and ranks the five most meaningful activities in their daily life. The participant also rates their occupational performance (COPM-P) and satisfaction (COPM-S) for each activity on a scale from 1 to 10.

In the second part of the interview, the older adult formulates a meaningful and relevant activity-based, person-centered goal for the intervention, based on one of the five prioritized activities identified in the previous step. The goal activity should be something the participant wants to perform or participate in but currently finds challenging or impossible. It must also be meaningful, relevant, and important for the participant’s well-being and QoL [42, 43]. An example of such a goal might be dressing independently, with the final goal being broken into smaller tasks that the participant practices with the nursing assistants during the 8 weeks of the Re-RAC intervention. Other examples might be moving independently to visit a neighbor in a different ward or participating in a social activity.

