A goal-oriented support plan with specific activities to achieve the goal is developed by the OT together with the participant. A nursing assistant such as the participant’s contact person at the RAC can also be involved depending on the needs of the participant. These activities may include the use of assistive devices, environmental adjustments, and modified activity behaviors, such as physical exercise or task-specific training. Multiple training activities may be included and are tailored to the individual’s daily capacity. The time allocated for each participant is customized based on their needs and the nature of the goal. The intensity of the intervention can range from 2 to 7 days per week, with training sessions occurring once or multiple times per day, and each session lasting up to a maximum of 30 min.

The intervention lasts 8 weeks. The OT introduces the nursing assistants, who will support the older adult during the intervention, to the person-centered goal and the planned activities in the support plan. The nursing assistants receive supervision on how to support the specific participant according to the previously described support plan for staff. The intervention aims for ongoing progress with an increasing level of difficulty. Thus, the nursing assistants can adjust the level of difficulty based on the participant’s progress in their occupational performance. Additionally, the OT, PT, or the participants can initiate adjustments to improve the performance.

After 8 weeks, the intervention concludes with a renewed COPM assessment [42, 43], during which the participant’s occupational performance and satisfaction with the performance, related to the person-centered goal, are evaluated.

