### Outcomes {12}

#### Primary outcome

The primary outcome is the mean change in occupational performance related to the prioritized activity, measured with COPM-P [42, 43], immediately after the 8-week intervention period. The comparison will be made between participants who have undergone the Re-RAC intervention and those receiving TAU.

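### The protocol names two different activities for scoring the primary outcome, the top-ranked activity and the goal activity, and never says they are the same

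*Protocol article*

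**What the plan says.** Four parts of the protocol article bear on which activity is scored.

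- **Primary outcome:** "The primary outcome is the mean change in occupational performance related to the prioritized activity, measured with COPM-P". The activity is singular but not identified further. Secondary outcomes uses the same term for COPM-S.
- **Measures, Canadian Occupational Performance Measure (COPM):** "Participants will rate their performance of and satisfaction with their highest-priority activity" on the 1–10 scale. Read plainly, this is the activity ranked first.
- **Implementation of the intervention, baseline interview:** "the participant identifies and ranks the five most meaningful activities in their daily life". Ratings are then taken for all five: "The participant also rates their occupational performance (COPM-P) and satisfaction (COPM-S) for each activity on a scale from 1 to 10". Goal setting follows at the same sitting, with the goal "based on one of the five prioritized activities identified in the previous step".
- **Implementation of the intervention, end of the 8 weeks:** the COPM is renewed and the participant's "occupational performance and satisfaction with the performance, related to the person-centered goal, are evaluated".

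Three other statements matter. The section on concomitant care {11d} says that controls also set a goal. The section on collection of outcomes {18a} says that follow-up mirrors baseline. Table 1 places the COPM at w0 and w9, and allocation at w–1.

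**The concern.** The top-ranked activity and the goal activity are chosen on different criteria. The ranking is by how meaningful the activity is. The goal must in addition concern something the participant currently finds hard or cannot do. The goal may be any of the five, so the two can be different activities, and the support plan trains toward the goal.

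Two consequences follow if the text stays as it is.

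1. Under the wording of the COPM measures section, a Re-RAC participant whose goal is ranked second to fifth is scored on an activity that the support plan does not target. Any benefit on the trained activity is then missed in that participant, and the between-group difference shrinks.
2. If baseline is taken from one section (rank 1) and follow-up from the other (the goal), the change score compares ratings of two different activities.

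This is the definition of the primary endpoint, stated in two ways in the current text. It is not a detail that a protocol article would normally leave to the analysis plan.

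**Working it through.** **Setting the sections side by side**

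| Section | Activity rated |
|---|---|
| Implementation, baseline interview | all five |
| Implementation, after 8 weeks | the goal activity |
| COPM measures | the highest-priority activity |
| Primary and secondary outcomes | the prioritized activity, not identified |

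The implementation section calls all five activities prioritized, so the wording of the primary outcome does not choose between rank 1 and the goal. No section requires the goal to be rank 1 or equates the terms.

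**The plan's own sample size**

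Inputs from Sample size {14}: difference 0.9, SD of change 1.3, two-sided α = 0.05, power 80%, dropout 25%, 43 per group, 86 in total.

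- Standardized difference: 0.9 / 1.3 = 0.692.
- Two-sample t-test (noncentral t): 33.74, so 34 per arm.
- 34 × 1.25 = 42.5, so 43 per arm and 86 in total. The stated figure is reproduced.
- Applying 25% dropout to 43 leaves 43 × 0.75 = 32.25, so 32 evaluable per arm. The results below are given for both 32 and 34.

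The conflict over the activity does not alter this arithmetic.

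**Illustration of dilution**

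Let f be the share of participants whose goal is not rank 1, and s the share of the effect that carries over to the untrained top-ranked activity. Neither is in the documents; both are assumptions. If rank 1 is scored, the expected difference is

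difference = 0.9 × [1 − f × (1 − s)].

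Power is from the two-sample t-test with SD 1.3.

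| f | s | Difference | Power, 32 per arm | Power, 34 per arm |
|---|---|---|---|---|
| 0 | – | 0.90 | 78% | 80% |
| 10% | 0 | 0.81 | 69% | 72% |
| 20% | 0 | 0.72 | 59% | 61% |
| 30% | 0 | 0.63 | 48% | 50% |
| 20% | 0.5 | 0.81 | 69% | 72% |
| 30% | 0.5 | 0.765 | 64% | 67% |

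Example: f = 20%, s = 0 gives 0.9 × 0.8 = 0.72. With s = 0.5 it is 0.9 × (1 − 0.2 × 0.5) = 0.81.

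If the goal activity is scored in everyone, f = 0 and this route to dilution disappears.

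**The case against.** The strongest reply is that this is a difference of terms with little practical effect. The participant chooses the goal and may usually choose the activity ranked first. All five activities are rated at baseline, so a baseline score exists for whichever activity is used, and follow-up is said to mirror baseline. The sentence on the 8-week COPM sits in the intervention description rather than the outcome definition, and it does not say that only the goal activity is re-rated. This weakens the mismatch between baseline and follow-up to a possibility. It does not say which rating enters the primary analysis.

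The power figures are also open to challenge. The 0.9 and the SD come from the feasibility study, and the protocol does not say which activity that study scored. If it scored the top-ranked activity, some discordance may already be inside the 0.9. The planned ANCOVA with baseline adjustment and multiple imputation is not modelled either. Both objections stand, so the figures are illustrative only.

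Two stronger readings are tempting and are not supported:

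- *Goal and rank 1 will often differ.* The documents give no frequency. Realism within the time frame is mentioned for how the goal is formulated, not as a rule for selecting the activity. The text shows only that the two can differ.
- *Scoring the goal, unlike scoring rank 1, lets the activity be chosen after allocation is known.* Ranking and goal come from the same interview at w0, and Table 1 has allocation at w–1. The timing affects both readings equally and is not a consequence of the conflicting terms.

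**Conclusion.** The contradiction is real and concerns the primary endpoint. The COPM measures section points to the top-ranked activity, the 8-week assessment points to the goal, and the outcome sections do not decide. It needs correcting whatever the frequency of discordance.

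The size of the harm is unknown. Under the worst-case assumption of no effect on untrained activities, and taking 0.9 as the effect on the trained activity, 10% to 30% discordance would bring power from about 78–80% down to between 69–72% and 48–50%. With half the effect carrying over, 20% and 30% discordance would leave 69–72% and 64–67%. These are conditional illustrations and not an estimate of the trial's power.

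**What to change.** Use one definition in Implementation of the intervention, Primary outcome, Secondary outcomes and the COPM measures section:

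- The primary outcome is the change in COPM-P for the goal activity recorded at the baseline COPM interview, in both arms, with that same activity re-rated at w9.
- COPM-S is scored on the same activity.

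The goal activity is workable because controls also set a goal, and it is the activity the support plan targets. The top-ranked activity named consistently would also give a unique endpoint, but it would keep the dilution described above.

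Confirm that the follow-up form re-rates the goal activity in both arms, and settle the definition before any outcome comparison. No interim analysis is planned, and data collection is expected to run to 31 December 2026, so there is time.

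**Cost:** a protocol and eCRF clarification, plus a check of follow-up ratings for participants enrolled since October 2024. Their baseline ratings should exist, since all five activities are rated; a follow-up rating of the goal activity has to be verified. Completing the baseline COPM before the envelope is opened is a separate timing question. It would change Table 1 for future participants only and is not needed to resolve this point.

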#### EQ-5D-5L

The EQ-5D-5L [44–46] is a widely used generic instrument for measuring health status. It consists of two parts: a descriptive system that assesses health across five dimensions (i.e., mobility, self-care, usual activities, pain/discomfort, and anxiety/depression), with each dimension having five response levels (i.e., no problems, slight problems, moderate problems, severe problems, and extreme problems/unable to). The second part is a visual analog scale (VAS), on which the participant rates their perceived health, ranging from 0 (the worst imaginable health) to 100 (the best imaginable health). In Re-RAC, the Swedish version of the interviewer-administrated version will be used. The EQ-5D-5L demonstrates strong psychometric properties across diverse populations, conditions, and settings [50].

#### World Health Organization Well-Being Index (WHO-5)

The WHO-5 is a widely used questionnaire designed to assess subjective psychological well-being. Each question is rated individually, with five statements evaluating how well they apply to the respondent over the past 14 days. Responses are scored on a scale from 5 (all the time) to 0 (none of the time), resulting in a total raw score ranging from 0 to 25 [47]. The questionnaire has demonstrated good internal and external validity when used with older adults [51]. In the Re-RAC study, the Swedish translation will be administered during a structured interview.

#### Accelerometer

A wrist-worn accelerometer with three axes (Actigraph GT3X +; ActiGraph, Pensacola, FL, USA) [52, 53] will be used to measure physical activity levels over two 7-day periods, one before and one after the intervention. Wrist-worn accelerometers have been shown to achieve high participant compliance [54]. Participants will also be provided with a diary covering the same time periods, in which to record the periods of time when the accelerometer is worn every day.

#### Participant experiences

Semi-structured individual interviews with 15–18 participants from the intervention group will be conducted to collect data on participant experiences. Participants from all participating RAC facilities will be asked to participate, and diversity in RAC facilities and participant characteristics will be striven for. The interviews will be conducted within 2 weeks following completion of the intervention. A study-specific interview guide will be used, focusing on participants’ experiences of the Re-RAC intervention, including their daily activities and perceptions of the professional team’s reception, support, and accessibility. Questions addressing the individual’s impact and participation in the intervention are also included. The interview guide was partially piloted during a feasibility study [28], with revisions made to improve the clarity of certain questions and terminology. Interviews will accommodate breaks as needed and will take place at a location chosen by each participant. A trained member of the research team will conduct the interviews, which will be audio-recorded and transcribed verbatim.

#### Staff experiences

Focus-group interviews will be conducted to capture staff experiences of Re-RAC. These experiences will be explored thorough six focus-group interviews (two at each RAC facility), with each group comprising five to eight staff informants [30]. A criterion-based inclusion approach will be employed, aiming for diversity of characteristics such as age, gender, education level, profession, and length of employment at the RAC facility. Recruitment of informants will continue until enough staff informants are available to form appropriately sized groups. A study-specific interview guide will be utilized, addressing experiences of the intervention in terms of its content, perceived benefits or drawbacks, reflections on the format and structure of the Re-RAC training, and how the intervention has influenced the staff members’ daily work. The interviews will be held in a meeting room at each RAC facility, and will be audio-recorded and transcribed verbatim. The same two moderators from the research group will conduct the interviews to ensure uniformity in facilitation. Before the first interview, the interview guide will be evaluated in terms of comprehensibility and relevance in a pilot interview.

#### Health-economic parameters

The health effect used in the health-economic evaluation will be measured in terms of QALYs. QALY gain will be calculated based on the EQ-5D-5L scores [44–46], comparing pre- and post-intervention data.

The cost estimates will include intervention costs and healthcare consumption costs. For the base case analysis, intervention costs will encompass all components of the intervention, including training, preparation, and execution. Costs for the training and preparation will be estimated based on information provided by the researcher responsible for the intervention. To monitor the extent to which each participant receives the intervention, and to capture adherence, all staff members will be required to complete a logbook located in each participant’s apartment every time they perform an intervention-related task, such as a training session with the participant. The logbook will include entries for the date, action/activity performed, time spent, and profession of the staff member who carried out the task. This information can also be partially monitored through the MCSS.

Healthcare resource utilization data will be retrieved from administrative systems covering primary care (e.g., NCS Cross or another relevant system), in- and outpatient care (e.g., InfoMedix PAS or equivalent), and municipal care (e.g., MCSS, TRESERVA, or similar systems) for the 3 months preceding and following the intervention period. Data on pharmacological prescriptions will be obtained from systems such as PASCAL, Läkemedel, or miniQ. All cost estimates will be costed using national Swedish tariffs. Medical records may also be consulted if necessary. The health-economic analysis is detailed in the health-economic analysis plan (HEAP), which is available from the researchers upon request.

